## Abstract

**Background:**

Although psycho-oncological interventions have been shown to significantly reduce symptoms of anxiety and depression and enhance quality of life, a substantial number of patients with advanced cancer do not receive psycho-oncological interventions tailored to their individual situation. Given the lack of reliable data on the efficacy of psycho-oncological interventions in palliative care settings, we aim to examine the efficacy of a brief, manualized individual psychotherapy for patients with advanced cancer: Managing Cancer and Living Meaningfully (CALM). CALM aims to reduce depression and death anxiety, to strengthen communication with health care providers, and to enhance hope and meaning in life. We adapted the intervention for German cancer care settings.

**Methods/Design:**

We use a single-blinded randomized-controlled trial design with two treatment conditions: intervention group (IG, CALM) and control group (CG). Patients in the CG receive a usual non-manualized supportive psycho-oncological intervention (SPI). Patients are randomized between the IG and CG and assessed at baseline (t_0_), after three (t_1_) and after 6 months (t_2_). We include patients with a malignant solid tumor who have tumor stages of III or IV (UICC classification). Patients who are included in the study are at least 18 years old, speak German fluently, score greater than or equal to nine on the PHQ-9 or/and greater than or equal to five on the Distress Thermometer. It is further necessary that there is no evidence of severe cognitive impairments. We measure depression, anxiety, distress, quality of life, demoralization, symptom distress, fatigue as well as spiritual well-being, posttraumatic growth and close relationship experiences using validated questionnaires. We hypothesize that patients in the IG will show a significantly lower level of depression 6 months after baseline compared to patients in the CG. We further hypothesize a significant reduction in anxiety and fatigue as well as significant improvements in psychological and spiritual well-being, meaning and post-traumatic growth in the IG compared to CG 6 months after baseline.

**Discussion:**

Our study will contribute important statistical evidence on whether CALM can reduce depression and existential distress in a German sample of advanced and highly distressed cancer patients.

**Trial registration:**

ClinicalTrials.gov NCT02051660

## Background

Worldwide, eight million people died from cancer in 2010 - an increase of 38 % over the last two decades [1]. Numerous studies have shown high levels of symptom burden and psychosocial distress associated with advanced cancer [2–6]. Psychological distress can range from normal adaptive emotions through to higher levels of severe and clinically significant symptoms that fulfill the standardized diagnostic criteria for adjustment disorder, anxiety disorders, or depression [7]. Studies demonstrate a total prevalence for any mental disorder of 32 % across all tumor settings and stages [8] and prevalence rates of 30–50 % for all mood disturbances including adjustment disorders and depression in palliative care settings [9, 10].

Many patients with advanced disease experience demoralization, existential and spiritual distress, or loss of dignity [6, 11, 12], reflecting a loss of hope and a diminished sense of meaning [13–16]. In addition, patients and caregivers are confronted with difficult treatment decisions in palliative care planning.

Various types of psycho-oncological interventions are associated with significant, small-to-medium effects on emotional distress and quality of life [17]. However, the majority of randomized controlled psycho-oncological intervention trials for cancer patients were tested in curative settings and predominantly included women [17]. Manualized meaning-based interventions to treat the psychosocial and existential distress in cancer patients have been developed and empirically tested [18–21]. Nevertheless, the number of evaluated and effective meaning-based psychotherapeutic interventions for advanced cancer patients is still small.

Psychotherapeutic interventions for individuals with advanced disease must be short-term and flexible enough to adjust to rapidly changing needs and clinical circumstances. Only two of eight interventions described in a review of meaning-based interventions for physically ill patients by Lemay and Wilson [18] are short-term [22, 23]. Although patients with advanced disease often find it difficult to attend sessions at a fixed time in a group setting, many existing psychotherapies for cancer patients are conceptualized as group therapies [24]. Group settings in palliative care can cause additional distress if patients are faced with the death of another group member. Moreover, very few interventions focus on addressing medical treatment situations in collaboration with the medical care team [25].

Although psycho-oncological interventions have been shown to significantly reduce symptoms of anxiety and depression and enhance quality of life [17], the majority of patients with advanced cancer do not receive psychotherapeutic interventions tailored to their individual situation. To address this deficit in palliative care, [name] and colleagues developed a brief, manualized individual psychotherapy for patients with advanced cancer: Managing Cancer and Living Meaningfully (CALM) [20, 26]. CALM aims to reduce depression and death anxiety, to strengthen communication with health care providers, and to enhance hope and meaning in life.

Given the lack of reliable data on the efficacy of psycho-oncological interventions in palliative care settings, we aim to examine the efficacy of CALM adapted for German cancer care settings compared to a non-manualized supportive psycho-oncological intervention (SPI) using a randomized control trial design (RCT).

## Methods

### Study design

In this bicenter German CALM study we use a single-blinded randomized-controlled trial design with two treatment conditions: intervention group (IG) and control group (CG). Patients are assessed during screening, at baseline (t_0_), after three (t_1_) and after 6 months (t_2_). Participants are randomized between the intervention and the control arm. Patients in the intervention group receive CALM, whereas patients in the control group receive a usual non-manualized supportive psycho-oncological intervention (SPI) to the same extent (frequency and duration) as CALM (Fig. 1).

**Fig. 1 Fig1:**
[figure not shown]
Study (RCT) design (German CALM RTC)

Our CALM RCT is conducted in two University Medical Centers: (a) the Outpatient Clinic for Psycho-oncology at the Department of Medical Psychology, University Medical Center Hamburg-Eppendorf and (b) the Outpatient Cancer Counseling Center at the Section of Psychosocial Oncology, Department of Medical Psychology and Medical Sociology, University Medical Center Leipzig. Our CALM RCT received ethics committee approval at both participating centers (Hamburg reference number: PV4435; Leipzig reference number: 143–14–14042014).

### Pilot phase

We conducted a pilot study prior to initiating the CALM RCT at the Outpatient Clinic for Psycho-oncology, Department of Medical Psychology, University Medical Center Hamburg-Eppendorf. We implemented this initial study phase over a 6-month period in order to test the standard operating procedures and to evaluate the feasibility of CALM in our setting. Patient recruitment followed the procedure outlined for the CALM RCT, except (a) patients were not screened for distress (DT/PHQ-9) to be considered eligible for the study and (b) there was no randomization: all participants were assigned to the intervention condition. Our pilot phase included an evaluation of each CALM therapy session and a semi-structured interview after completing at least three therapy sessions. The semi-structured interview focused on how participants experienced or evaluated (a) the overall CALM therapy; (b) each of the four CALM dimensions; (c) the therapeutic alliance, and (d) the structure and timeframe of CALM.

### Description of the experimental (CALM) and control (SPI) interventions

#### Managing Cancer and Living Meaningfully (CALM)

Patients in the IG receive the brief, individual, manualized CALM intervention [20, 26]. This semi-structured psychotherapeutic intervention was designed for patients with advanced cancer and is based on empirical research results, clinical observations and theoretical concepts of supportive-expressive, existential, and psychodynamic therapy as well as stress- and problem-solving trainings. CALM covers the following four domains:*Symptom management and communication with health care providers*: Within this domain, cooperation and improvement of communication with health care providers, and help regarding medical decision-making to ensure best care and control of symptoms are addressed;*Changes in self and relations with close others*: Within this domain, supporting the adjustment of self-esteem and identity to cancer-related changes, also in regard to relationships with close others, and sustaining and providing required care and support are addressed;*Spirituality, sense of meaning and purpose*: Within this domain, understanding the individual meaning of suffering and dying, and evaluation of priorities and goals facing an advanced disease are addressed;*Preparing for the future, sustaining hope and facing mortality*: Within this domain, acknowledgment of anticipatory fears, balancing life and death, planning advanced treatment, and preparing the process of dying are addressed.

In each CALM session, the patient decides which one of these domains and to what extent each domain is covered depending on their current concerns and supportive care needs. During a period of 6 months, patients in the IG receive up to eight sessions of individual therapy, each lasting 50 min.

#### Non-manualized supportive psycho-oncological intervention (SPI)

Patients in the CG receive a non-manualized supportive psycho-oncological intervention, which is regularly conducted by psychotherapists at both study centers, the Outpatient Cancer Counseling Center at the Section of Psychosocial Oncology, Department of Medical Psychology and Medical Sociology, University Medical Center Leipzig, and the Outpatient Clinic for Psycho-oncology at the Department of Medical Psychology, University Medical Center Hamburg-Eppendorf. The therapeutic approach is based on an integrative approach consisting of psycho-oncological counseling, information, crisis intervention as well as supportive individual therapy. As IG patients, CG patients receive up to eight sessions of individual therapy during a period of 6 months, each session lasting 50 min.

### Participants and procedure

We are recruiting patients at both study centers in Hamburg and Leipzig as well as in local university cancer care units and external cancer care facilities. Patients with advanced cancer are contacted by a study research assistant and assessed for eligibility by using the depression module of the Patient Health Questionnaire (PHQ-9) [27–29] and the Distress Thermometer (DT) [30] as screening tools. Patients fulfilling the inclusion criteria are subsequently invited to a face-to-face interview with the research assistant to receive comprehensive information about our RCT. Further inclusion and exclusion criteria are evaluated. The study research assistant conducts the Short Orientation Memory Concentration test (SOMC) [31, 32] and the depression section of the Structured Clinical Interview for DSM-IV (SCID-I) [33] to evaluate whether patients meet the criteria for a major depressive disorder. If patients meet all inclusion criteria and are willing to participate, they are randomized (single-blinded) in either the intervention or the control group. At the end of the face-to-face interview patients receive the baseline questionnaire with a prepaid envelope and are asked to return it within 2 weeks.

All patients provide written informed consent prior to participation. Principles of good research practice are strictly adhered to in this project including data and patients’ privacy protection. Patients can withdraw their informed consent at all times without having to fear any disadvantage in their medical or psychological treatment. In case patients decide not to participate in the study or to withdraw informed consent, reasons as well as basic demographic and medical characteristics (age, sex, diagnosis, date of diagnosis, educational background) are documented on a voluntary basis. These data will be used to conduct non-responder analyses and identify a potential sample bias.

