### Randomization procedure

Study participants are randomly assigned to receive either CALM or SPI. The random allocation sequence (randomization list) was generated by the Institute of Medical Biometry and Epidemiology at the University Medical Center Hamburg-Eppendorf. Randomization is stratified according to sex. After a patient gives written informed consent for study participation, a study research assistant reports the patients’ initials, date of birth and sex to a blinded research assistant at the University Medical Center in Leipzig. The research assistant includes the patient in the randomization list and informs the research assistant about treatment allocation (CALM or SPI). No CALM study member and research assistant has access to the randomization list. The patient is not informed about their treatment condition.

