#### Statistical analysis

For the final analyses we will use an intention-to-treat approach (ITT) and compare patients in the assigned treatment groups. Main analyses to evaluate efficacy based on primary (depression) and secondary outcomes at 6 months follow-up (primary endpoint) will be performed using analysis of covariance (ANCOVA). In case of missing outcome data at the primary endpoint, we use the last observation carried forward (LOCF) method. Controlling for baseline test scores as well as demographic and disease-related characteristics, we hypothesize that the mean depression score in the IG will be lower than the one in the CG. Other analyses will include a mixed model approaches (to examine changes over time), regression analyses (controlling for additional factors), and exploratory analyses (of treatment effect modifiers).

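### Baseline scores on nine scales come from a take-home form that may be completed, or lost, after randomisation, yet they serve as ANCOVA covariates

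*Protocol article*

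**What the plan says.** Participants and procedure describes the interview, the eligibility checks, and then allocation: "If patients meet all inclusion criteria and are willing to participate, they are randomized (single-blinded) in either the intervention or the control group". The next sentence says that, at the end of that interview, "patients receive the baseline questionnaire with a prepaid envelope and are asked to return it within 2 weeks".

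Randomization procedure gives the trigger: "After a patient gives written informed consent for study participation, a study research assistant reports the patients’ initials, date of birth and sex" to an assistant in Leipzig, who replies with the allocation. It adds: "The patient is not informed about their treatment condition".

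Baseline assessment repeats that the form is handed over at the end of the interview. By its text, the form holds every primary and secondary outcome except PHQ-9, DT and GAD-7. Table 1 marks nine instruments under t0: DS, BFI, MSAS-SF, FACIT-SP, DADDS, PTGI, ECR-M16, QUAL-EC and CCS. It places PHQ-9, DT and GAD-7 in the screening/interview column and gives BDI-II marks at t1 and t2 only.

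Statistical analysis specifies an intention-to-treat ANCOVA at 6 months for primary and secondary outcomes, "Controlling for baseline test scores as well as demographic and disease-related characteristics". LOCF is stated for missing outcomes at the primary endpoint.

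**The concern.** ANCOVA on a baseline score assumes that treatment cannot have touched that score. A form completed at home over two weeks, with allocation tied to consent and not to receipt of the form, does not guarantee this. Two things can go wrong.

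- **Contamination.** If a patient fills in the form after a first session, the score may already carry some early response. Adjusting for it then moves the estimated effect.
- **Loss after randomisation.** A form that never comes back leaves a randomised patient without the covariate. A standard ANCOVA drops that patient, despite the intention-to-treat label. If the same patient also has no t1 or t2 value, LOCF has nothing to carry forward on that scale.

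Several of the nine scales measure the named secondary hypotheses on fatigue, spiritual well-being, meaning and posttraumatic growth.

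**Working it through.** **1. Sequence, from the sections side by side.**

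- Lower bound for allocation: written consent (Randomization procedure).
- Handover of the form: end of the interview (Participants and procedure; Baseline assessment).
- Return of the form: by post, up to 2 weeks later.
- First session: no date given.

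That allocation precedes handover is suggested by the order of the sentences but not stated. The point does not depend on it: even if allocation followed handover, the form could still be completed later, because allocation does not wait for its return.

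**2. Which baselines are exposed.**

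- Exposed: the nine scales listed under t0 in Table 1.
- Not exposed: PHQ-9 and DT, taken before the interview, and GAD-7, placed at screening/interview.
- Unclear: BDI-II. The Baseline assessment text would put it in the form, whereas Table 1 gives it no baseline at all.

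**3. The plan's own sample size.** Inputs from Power calculation: d = 0.405, r = 0.70, SD = 7.4, completion p = 0.60, compliance c = 0.80. Alpha and power are not stated; two-sided 0.05 and 80% are assumed, and they reproduce the stated figures.

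- n = 2(1.960 + 0.842)² × (1 − 0.70²) / 0.405² + 1 = 49.8, rounded up to 50 per group.
- Recruited per group: 50 / (0.60 × 0.80²) = 130.2, rounded up to 131, or 262 in total.

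Both stated figures are reproduced and are not in dispute.

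**4. Illustration: missing t0 forms, those patients dropped.** The non-return fraction m is assumed.

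- Effective n per group = 131 × 0.60 × 0.64 × (1 − m).
- Power = Φ{0.405/√(1 − 0.70²) × √[(n − 1)/2] − 1.96}.

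| m | Forms missing of 262 | Effective n per group | Power |
|---|---|---|---|
| 0 | 0 | 50.3 | 80% |
| 5% | 13 | 47.8 | 78% |
| 10% | 26 | 45.3 | 76% |
| 20% | 52 | 40.2 | 71% |

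This takes non-return to be unrelated to later drop-out. If those who do not return t0 are mostly among the 40% expected to be lost anyway, the extra loss is smaller.

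**5. Illustration: t0 already carries part of the effect.** The fraction f of a 3-point effect already present at t0 is assumed, with slope 0.7 (equal SDs).

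- Adjusted estimate = 3 × (1 − 0.7f).
- f = 5%, 10%, 20% gives 2.90, 2.79 and 2.58 points.
- Power, with n − 1 = 49 and residual SD 7.4 × √0.51, is 77%, 74% and 68%.

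Steps 4 and 5 use BDI-II planning values. They describe an outcome with that d and r whose baseline comes from the posted form. The nine scales have other ranges, and the article gives no d or r for them.

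**The case against.** The strongest reply is that the risk is narrow and partly inferred.

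- **Order.** A reader might infer that the article states the form is handed out after allocation, by an assistant who already knows the arm. It fixes only the time of handover and the earliest time of allocation. This stands: the supportable wording is that the form may be completed after randomisation.
- **Knowledge of allocation.** A reader might also infer that patients answer in the light of their arm. The form is self-completed by patients who are not told their condition, so this route is weak.
- **Early therapy.** Overlap with a first session is possible but not documented. Three or four sessions in three months is about one every three to four weeks, so about one session at most would usually fall in the return window. Both arms receive individual therapy of the same frequency and duration, so an early difference between arms is likely to be small.
- **Scope.** A reader might take all ANCOVA baselines to be compromised, including that of the primary outcome. A PHQ-9 baseline for depression is untouched.
- **Size.** An early difference between arms of, say, half a point has no source in the article, and expressing it as a share of the 3-point BDI-II effect does not carry over to the other scales.
- **Condensed reporting.** Handling of missing covariates, and scheduling detail, may stand in a full protocol or SAP. Silence on those is not held against the article. What remains is the collection sequence that the article does state.

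**Conclusion.** The point holds in limited form. As described, the procedure allows the t0 scores of nine mostly secondary instruments to be completed after randomisation, possibly after a first session, or to go missing after randomisation, and then uses such scores as covariates. PHQ-9, DT and GAD-7 are not affected. BDI-II is affected only if the Baseline assessment text prevails over Table 1.

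The direction and size of any bias cannot be derived from the document. The power figures of about 78% to 71% rest on assumed non-return of 5% to 20%, on dropping those patients, and on the planned d and r. They show scale and predict nothing. The documents do not support the stronger conclusion that the depression analysis is biased or that unblinded answering is the mechanism. This is a low-cost improvement worth making.

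**What to change.** 1. Have the t0 form completed and handed in at the interview before the assistant requests the allocation. If that is too burdensome, require it at minimum before the first session.
2. Record the completion date on every t0 form and the date of the first session.
3. State that randomised patients stay in the ANCOVA when t0 is missing or dated after the first session. Treat such a score as missing and impute the baseline covariate (mean or multiple imputation). This is a fallback: when non-return happens after allocation it may differ between arms, and imputation cannot fully repair that.
4. Reconcile the Baseline assessment text with Table 1 on whether BDI-II is measured at baseline.

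The cost is a longer interview, or a delay in allocation that could reach the 2-week return window if allocation waits for the post. Recruitment is already under way, so the baseline procedure would differ between earlier and later patients. The date of the change should be recorded.

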### Eligibility for study participation

#### Study inclusion criteria

We include patients with (a) a malignant solid tumor who have (b) tumor stages of III or IV in accordance to the UICC classification, including advanced disease in case of sarcoma, melanoma and endocrine tumors, which implies average life expectancies between 12 and 18 months. Patients who are included in the study (c) are at least 18 years old, (d) speak German fluently, (e) score greater than or equal to nine on the PHQ-9 or/and greater than or equal to five on the Distress Thermometer (DT). It is further necessary that (f) there is no evidence of severe cognitive impairments in the patient’s records or indicated by his or her physician or oncologist, as this would interfere with the practical performance of the psychotherapeutic interventions (CALM and SPI).

#### Study exclusion criteria

During the face-to-face interview the study research assistant evaluates the following exclusion criteria: (a) deficits in communication, (b) lack of willingness or inability to attend all of the necessary therapy sessions and (c) acute suicidality (concrete suicidal thoughts and/or plans, in which case psychiatric care is provided immediately). Patients who (d) score less than 20 points on the Short Orientation-Memory-Concentration test (SOMC) or (e) show a level of less than 70 on the Karnofsky index are excluded, because life expectancy in that case is expected to be less than 6 months [34, 35]. Patients will be further excluded from the study in case they receive parallel psychotherapy. Previous experiences with psychotherapy as well as concurrent psychopharmacological treatment are documented but are no reasons to be excluded from study participation.

